#### Tinnitus Questionnaires

- The *Tinnitus Handicap Inventory (THI)* has 3 subscales: a functional subscale (11 items), an emotional subscale (9 items) and a catastrophic subscale (5 items).

- *The Tinnitus Questionnaire (TQ)* encompasses 52 questions on tinnitus related to: emotional distress, cognitive distress, intrusiveness, auditory perceptual difficulties, sleep disturbance and somatic complaints.
- *The Tinnitus Burden Questionnaire*: This questionnaire contains 12 questions on the severity and character of tinnitus described by subjects.

#### Cost utility diary:

Subjects are asked to keep a monthly diary involving physical complaints and costs regarding general health and their hearing aid. After two years, the subjects will complete the cost utility diary once per three months. Also this questionnaire will address sick leave and other labor productivity related issues. The questionnaires are developed for this study in consultation with a specialist in Economics in Health Care, affiliated with the Julius Center for Health Sciences and Primary Care, UMC Utrecht. The outcomes of this questionnaire will represent the *numerator* of the cost utility ratio.

The questionnaires will be filled out by patients starting on the day of surgery in the CI group and in group B and C after patients made their definitive choice for BAHA, CROSS or no treatment. Subjects are asked to specify complaints and/or costs in the diary. All subjects will be reminded on regular basis by email to keep filling in the diary.

The HUI3 and EQ5D questionnaire outcomes will be plotted in a graph in which the area under the curve will reflect Quality Adjusted Life Years (QALYs). Also, these data will produce the *denominator* of the cost utility ratio.

The patient can choose if he/she would like to fill in the subjective questionnaires digitally or in a paper version. This will be verified in the Informed Consent Form. The patient is able to change his/her preference during the study period. All questionnaires that cannot be transformed to digital questionnaires (SSQ, VAS, TTO, EQ5D, Tinnitus Burden Questionnaire) will be filled out by all patients on paper.

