# 1. INTRODUCTION AND RATIONALE

## ***1.1 Introduction***

The present study was initiated by [name]. [name] (University Medical Center Utrecht) who approached [name] (Cochlear® Benelux NV) in 2013 for a research collaboration on adult cochlear implantation in patients with single-sided deafness (SSD) with the idea of using a Randomised Controlled Trial (RCT) to compare cochlear implantation to current clinical practice with either a Bone-Anchored Hearing Aid (BAHA) or a Contralateral Routing of Sound System (CROSS).

Patients who develop SSD become aware of the importance of hearing with two ears in everyday listening environments. Current treatment modalities for SSD (i.e. BAHA or CROSS) are effective in restoring sound awareness to the deaf side, but they do not provide benefits with regard to sound localization and improvement in speech perception in noise. These limitations may be overcome by providing a cochlear implant (CI) to the affected ear. The main objective of our study is to evaluate the clinical outcome after cochlear implantation compared to standard health care therapy with either CROSS or BAHA in patients with SSD.

There is no high quality research on the topic of cochlear implantation for patients with single-sided deafness yet. Although current available evidence is limited, the first results of non-randomised trials are promising. In patients with SSD, cochlear implantation leads to an improved quality of life, better speech perception, localization of sounds and reduction of tinnitus complaints compared to BAHA, CROSS or no treatment (Arndt 2010; vd Heyning 2008; Távora-Vieira 2013). Conversely, the significant costs of cochlear implantation over CROSS or BAHA limit the potential use of this modality in patients with SSD. Further high quality research is certainly necessary to provide compelling evidence of sufficiently large benefits of cochlear implantation over CROSS or BAHA in patients with SSD to justify the additional costs. Therefore, our study will be conducted as a RCT to control for biases when assigning subjects to one of three study groups. RCTs are the most rigorous experimental design for establishing the effectiveness of one intervention compared with another (Woolf 1990).

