## **4.2 Inclusion criteria**

- Patients aged 18 or older.
- Acute onset of postlingual SSD, defined as onset unilateral hearing loss between  $\geq 3$  months and  $\leq 10$  years before time of inclusion.
- Hearing measurements:
  - Pure Tone Audiometry of the deaf ear, defined as thresholds of 70 dB or higher on frequencies 0,5 – 4.0 kHz (average).
  - Normal hearing on the contralateral ear, defined as pure tone audiometry thresholds of 30 dB or less on frequencies 0.5 – 4.0 kHz (average).
  - Air bone gap  $\leq 10$  dB.
- Normal function of middle ear (i.e. no acute middle ear infections or tympanic membrane perforations).
- Dutch language proficiency.
- Willingness and ability to participate in all scheduled procedures outlined in the protocol.
- General health allowing general anaesthesia for the potential surgical implantation of a CI or BAHA.
- Patients covered by the Dutch health insurance.
- Patients should agree to be implanted with a CI or BAHA.
- Informed consent understood, filled out and signed by patient.
- Patients are not allowed to participate in another ongoing research study related to SSD or cochlear implantation.

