##### Subjective

- Self-reported benefits in everyday listening situations assessed with the Speech, Spatial and Qualities Hearing Scale (SSQ); 63 questions
- Quality-of-life (QoL) questionnaire score:
  - Health Utilities Index 3 (HUI3); 17 questions
  - Glasgow Benefit Inventory (GBI); 18 questions
  - Abbreviated Profile of Hearing Aid Benefit (APHAB); 24 questions
  - Time Trade Off (TTO); 1 question
  - Visual Analogue Scale (VAS); 2 questions
  - Euro-QoL 5D (EQ5D); 6 questions
  - Hospital Anxiety and Depression Scale (HADS); 14 questions
- Tinnitus questionnaires
  - Tinnitus Handicap Inventory (THI); 25 questions
  - Tinnitus Questionnaire (TQ); 52 questions
  - Tinnitus Burden Questionnaire; 12 questions
- Cost utility
  - Costs utility diaries on monthly basis (after 2 years: 3-monthly basis)

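### The cost-utility numerator rests on a patient diary, with no named source for implant, surgery and fitting costs and a start date that differs by arm and contradicts Section 5.1

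*Protocol*

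**What the plan says.** Section 6.3.2 fixes both halves of the ratio. Of the diary it says: "The outcomes of this questionnaire will represent the *numerator* of the cost utility ratio". The denominator is the QALY total, taken as the area under the HUI3 and EQ5D curves.

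On content: "Subjects are asked to keep a monthly diary involving physical complaints and costs regarding general health and their hearing aid". It continues: "Also this questionnaire will address sick leave and other labor productivity related issues". The patient supplies the entries: "Subjects are asked to specify complaints and/or costs in the diary". The diary items are not reproduced, but "The questionnaires are developed for this study in consultation with a specialist in Economics in Health Care".

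The Summary and the endpoint list in Section 6.1.2 name only the diary under cost utility. Section 8 refers back to Section 6.3.2.

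Two start dates are given. Section 6.3.2 begins the diary at surgery in the CI group, and in groups B and C once the patient has settled on BAHA, CROSS or nothing. Section 5.1 begins it on the day after inclusion for all patients.

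On why cost matters, Section 1.1 says that "the significant costs of cochlear implantation over CROSS or BAHA limit the potential use of this modality".

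**The concern.** The largest cost difference between the arms should lie in the implant, the operation, the admission and the fitting. A diary that patients fill in is a weak source for these, because nothing in the protocol suggests that patients see their prices, and no other source is named. A numerator built as written could leave out most of the contrast that the cost-utility analysis exists to measure.

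The start rule adds a second problem. If costs accrue from different points after randomisation in different arms, while utilities are measured from randomisation in all, numerator and denominator cover different periods and the arms are not compared like with like.

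At stake is the ratio itself. Section 1.1 asks whether the benefits justify the additional costs, and Section 6.8 foresees that insurers may change reimbursement after the study.

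**Working it through.** The protocol gives no cost, unit price or cost-utility ratio, so there is no stated figure to reproduce. The check compares the text and then works out direction only.

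**1. Cost sources named.**
- Summary: diary.
- Section 6.1.2: diary.
- Section 6.3.2: diary, defined as the numerator.
- Section 8: cross-reference to Section 6.3.2.
- Hospital records, insurer claims, device prices, unit costs and costing perspective: not named anywhere.

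**2. Time windows.**
- CI group: Section 3 places implantation directly after randomisation. Under Section 6.3.2 the diary starts on the day of surgery. The anaesthetic and CI-team evaluations that Section 5.1 describes for this group come before it.
- Groups B and C: Section 3 gives two test periods of 6 weeks, so the choice comes at about 12 weeks. Under Section 6.3.2 the diary starts after that. Over five years the gap is 12/260 = 4.6% of follow-up, and over the first two years 12/104 = 11.5%.
- Utilities: Section 5.1 measures HUI3 and EQ5D at randomisation in all arms.
- Section 5.1 diary rule: the day after inclusion for all, with inclusion and randomisation taking place together. Under this rule the gaps largely close. The two sections cannot both be followed.

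**3. Direction if procedure costs are missing.** Let C_CI, C_BAHA and C_CROSS be the provider-side cost per treated patient. Section 4.4 predicts that, of the 90 patients in groups B and C, 40 end with BAHA, 30 with CROSS and 20 with nothing. The omitted CI-minus-control increment per patient is

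D1 = C_CI − (40/90)·C_BAHA − (30/90)·C_CROSS = C_CI − 0.444·C_BAHA − 0.333·C_CROSS.

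If CI costs more than each comparator, as Section 1.1 indicates, D1 exceeds (1 − 0.444 − 0.333)·C_CI = 0.222·C_CI, so it is positive. Leaving it out understates the CI increment.

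Illustration on assumed inputs: with BAHA at 0 to 75% and CROSS at 0 to 50% of the CI cost, D1 runs from 1 − 0.333 − 0.167 = 0.50 up to 1.00 of C_CI.

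**4. Direction of the window effect under Section 6.3.2.** Let W be the post-randomisation costs before CI surgery, and T the costs in groups B and C up to the device choice, including the test devices. The omitted increment is D2 = W − T. The T part understates the costs of groups B and C and so works against CI. Imaging and eligibility work-up precede randomisation in every arm and should cancel.

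**5. Net.** The total omitted increment is D1 + D2. It favours CI when D1 + W exceeds T. The protocol gives none of these amounts.

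**The case against.** The best defence is that the diary has not been seen. It covers costs of general health and of the hearing aid, a health economist helped to design it, and in the CI group it opens on the day of surgery. It may record operations, admissions and visits as resource use, to be priced later. Valuation, perspective and linkage with hospital data are often left to an analysis plan, which is not at hand. Implant and surgery are one-off events that can still be costed at the end. Section 2 lists cost utility last, as a further point of interest, and the primary outcome is untouched.

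Much of this stands, and it rules out several stronger readings:
- A reader might infer that the diary cannot contain the procedure costs. The items are not shown, so this is not established. Nor does the text say that the diary is the only source; it simply names no other.
- A reader might infer that insurer or hospital pays for the study CI. Section 4.2 requires only "Patients covered by the Dutch health insurance". Section 6.8 says BAHA and CROSS are reimbursed and implies that CI for SSD is not yet. The payer of the study CI is not stated.
- A reader might attach a euro amount per QALY. Both the omitted cost and the QALY gain would have to be assumed.
- A reader might take every omission as favouring CI. Leaving out the test periods does the opposite.

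The defence does not remove the core. Section 6.3.2 is a stated definition, and an analysis plan that follows it inherits it. Even a resource-use diary needs a source for device prices and unit costs. The conflict over the start date exists whatever the diary items are.

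**Conclusion.** The point holds as a risk of bias that the protocol writes into its own definition. The numerator is tied to a patient-completed diary, and no route is given for device, surgery, admission, CI-team and fitting costs. If those costs are indeed missing, the procedure-cost omission understates the CI increment. That sign rests on the Section 1.1 statement that CI costs more and on the treatment split predicted in Section 4.4. The size cannot be derived from the protocol; the range of 50 to 100% of the CI procedure cost is an illustration on assumed cost ratios.

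Separately, and without any assumption about the diary items, Sections 5.1 and 6.3.2 contradict each other on when the diary starts. The Section 6.3.2 rule gives cost windows that differ by arm and do not match the utilities. The omitted test periods partly offset the first bias, by an amount that is also unknown.

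The protocol should be amended on both counts. The effectiveness analyses are not affected.

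**What to change.** Reconcile Sections 5.1 and 6.3.2 so that costs are counted from randomisation in all three groups, matching the utilities.

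Redefine the numerator in Section 6.3.2 as the sum of two parts:
- provider-side resource use from hospital records, valued at unit costs: device, surgery, admission, work-up after randomisation, fitting, revisions and test-period devices;
- diary items: other care, out-of-pocket costs and productivity loss.

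Section 5.1 places follow-up of CROSS patients with their own audiologist, so the centre's records will not hold all of that care. Take it from the diary.

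The cost is one records extraction and a unit-cost table. The extraction adds no patient burden; under the Section 5.1 start, groups B and C would keep the diary during the test periods. The ratio will probably be less favourable to CI. If the sponsor already intends this costing, a short statement in Section 6.3.2 and a single start date would settle the matter.

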### 3. STUDY DESIGN

The study design is illustrated in Figure 1 (next page). Patients participate after Informed Consent is obtained. In the dark blue squares of the figure, the different subsequent steps after inclusion are noted. The different time-points for follow-up are outlined in the yellow squares.

When subjects are selected, the following characteristics will be documented in a Case Report Form: gender, age, highest level of education, duration of unilateral deafness, anatomical and aetiological issues as well as psychological and motivational attributes.

After inclusion, subjects will be randomly allocated (see section 6.2 Randomisation, blinding and treatment allocation) to one of three treatment groups:

1. Group A: cochlear implantation
2. Group B: 6-week during test periods with first BAHA, then CROSS
3. Group C: 6-week during test periods with first CROSS, then BAHA

Subjects in group A, the cochlear implantation group, will receive a CI directly after randomisation. The device will be programmed 3-7 weeks after surgery, which is standard CI care.

Subjects in group B shall start with a 6 weeks during test period with a BAHA on a headband. After the 6 weeks, these subjects switch to another test period of 6 weeks with a CROSS. In group C, subjects start with a CROSS and after their first 6-week test period they switch to a test period with a BAHA on headband for 6 weeks. After these two test periods, three questionnaires will be filled out (SSQ, APHAB and GBI; see Section 6.1.2. Secondary study parameters/endpoints). The participants in groups B and C complete both test periods after 12 weeks. The reason for this cross-over is to control for bias caused by the order effect, which means that participants will judge the second modality influenced by their experience using the first modality. Since we have created two groups with the opposite sequence, the order effect is eliminated. After completing both test periods, subjects will be seen in our clinic and have to choose for further treatment with either CROSS, a definitive surgically implanted BAHA or no treatment (if they found none of the modalities helpful).

Figure 1: study design

[figure not shown]

Legend: SSD: single-sided deafness, N: number of subjects, CI: cochlear implant; BAHA\*: bone-anchored hearing aid on headband, BAHA (def): definitive surgically implanted BAHA, CROSS: contralateral routing of sound system, FU: follow-up.

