## 5. TREATMENT OF SUBJECTS

### ***5.1 Investigational product/treatment***

Before study inclusion, subjects will receive standard workup for the diagnosis SSD. This ENT workup includes a clinical history and interview, otologic examination, audiological testing and a MRI-scan for auditory nerve evaluation. Additionally, to determine eligibility for cochlear implantation, a CT-scan will be made to visualize the anatomy of the mastoid. When the diagnosis SSD is sure, all inclusion criteria are met and anatomy permits cochlear implantation, inclusion and randomisation will take place.

Subjects will be asked to read and sign the Informed Consent form presented by the patient's ENT-surgeon before randomisation. This physician will fill in a Demographics Form to gather subject information.

Baseline evaluation for gathering study related data will take place locally at randomisation:

- Pure tone audiometry
- Speech audiometry (CVC [consonant-vowel-consonant] score in quiet)
- Questionnaires: SSQ, HUI3, GBI, APHAB, TTO, VAS, EQ5D, HADS, and Tinnitus questionnaires.

The patients will be asked to fill in a monthly costs diary starting on the first day after inclusion until the end of the second year of the study. From then on, they will complete the costs diary once per 3 months.

For all patients in group A (CI group) and those in group B or C preferring BAHA implantation preoperative medical evaluation will be carried out locally by the anaesthesiologist and includes a determination of general health status and suitability for surgery. Subjects in the CI group will also be evaluated by the center's Cochlear Implant Team, as is standard care for cochlear implantees. The standard surgical procedures developed for placement of the BAHA and the internal components of the CI will be followed. Specific procedures for implanting of the devices will be left to the discretion of the surgeon.

The first evaluation visit will occur approximately 3 to 7 weeks after surgery in the CI group to custom fit the processor software. It will be programmed for optimal speech perception, based on individual subject preferences.

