#### Quality-of-life questionnaires

- The *Health Utilities Index 3 (HUI3)* is a measure of general health status. It contains questions on eight domains: vision, hearing, speech, ambulation, dexterity, cognition, emotion and pain.
- *Time Trade-off (TTO)*: comprises one question about how many years of the life patients are living at the moment, they would sacrifice for living with perfect hearing for the rest of their days.
- *Visual Analogue Scale (VAS)*: comprises two 10cm scales on which patients can rate their hearing and health.
- *Euro-QoL5D*: is a measure of general health status. It contains questions on: mobility, self-care, daily activities, pain/complaints, anxiety/depression.
- The *Abbreviated Profile of Hearing Aid Benefit (APHAB)* is a 24 item, self assessment, disability based inventory to document the outcome of a hearing aid fitting and evaluate the fitting over time. The inventory yields scores on subscales for ease of communication, listening under reverberant conditions, listening in background noise and aversiveness of sound.
- The *Glasgow Benefit Inventory (GBI)* is a measure of patient benefit developed especially for otorhinolaryngological interventions (Robinson 1996). It is validated to measure outcomes on health status after otorhinolaryngological procedures. It measures QoL in three domains: social, general and physical. The domains score on a scale of -100 to 100 (minimum versus maximum benefit, respectively).
- *Hospital Anxiety and Depression Scale (HADS)*: a fourteen item screening tool for anxiety and depression in non-psychiatric clinical populations.

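### Section 6.3.2 starts the cost diary at a different time in each arm, contradicting sections 3 and 5.1; if followed, it gives unequal cost windows for the cost-utility ratio

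*Protocol*

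**What the plan says.** Three places in the protocol bear on when the diary starts.

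- Section 5.1 applies one rule to everyone: "The patients will be asked to fill in a monthly costs diary starting on the first day after inclusion". It runs monthly to the end of year two and every three months after that.
- Section 3 counts the first two years from randomisation and asks for a monthly diary throughout them, which fits section 5.1.
- Section 6.3.2, under the heading for the cost utility diary, has it filled out "starting on the day of surgery in the CI group and in group B and C after patients made their definitive choice" of BAHA, CROSS or no treatment.

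On timing, section 3 says that group A "will receive a CI directly after randomisation", with no number of days or weeks. For the other arms, "The participants in groups B and C complete both test periods after 12 weeks", and the choice of treatment follows.

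On use, section 6.3.2 says of the diary: "The outcomes of this questionnaire will represent the *numerator* of the cost utility ratio". For the denominator, "The HUI3 and EQ5D questionnaire outcomes will be plotted in a graph in which the area under the curve will reflect" QALYs. Section 5.1 places the baseline HUI3 and EQ5D at randomisation. Section 8 refers the reader to section 6.3.2 for the cost-utility analysis.

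**The concern.** A site cannot follow both start rules, and the conflicting one stands in the section to which section 8 points for the cost-utility analysis. Under section 6.3.2 the cost clock starts at an event that depends on the arm: surgery in group A, the patient's choice in groups B and C. The follow-up visits and the utility baseline run from randomisation in all arms. The cost window would then differ between arms, and in each arm it would start later than the utility data by a different amount.

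The diary covers health care and hearing-aid costs, sick leave and productivity. For groups B and C the missing stretch holds the two device test periods and the evaluations at 6 and 12 weeks. For group A it holds whatever falls between randomisation and surgery, possibly including the preoperative evaluation.

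The loss would be one of data collection. A diary that was never issued cannot be recovered by an analysis plan. The multiple imputation promised in section 8 has little to work from when a period is missing by design for every subject in an arm. Cost utility is a stated objective, and section 6.8 links a finding in favour of CI to possible changes in reimbursement.

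**Working it through.** The protocol states no figure for the length of the cost window, so there is nothing to reproduce. The check uses the protocol's own times.

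**Inputs**
- Diary start under section 5.1: first day after inclusion, all groups. Section 5.1 has inclusion and randomisation take place together, so this is treated as week 0.
- Diary start under section 6.3.2, groups B and C: after the definitive choice, which follows two 6-week test periods (section 3). Earliest time: 6 + 6 = 12 weeks.
- Diary start under section 6.3.2, group A: day of surgery, *s* weeks after randomisation. The protocol gives no *s*. Assumed values: 0, 4, 8 and 12 weeks.
- Horizon: months after randomisation, converted at 365.25 / 7 / 12 = 4.348 weeks per month.

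**Step 1: time lost in groups B and C under section 6.3.2.** Share lost = 12 / T, with T the horizon in weeks.

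| Horizon | T (weeks) | Covered, T − 12 | Lost |
|---|---|---|---|
| 6 months | 26.1 | 14.1 | 46.0% |
| 12 months | 52.2 | 40.2 | 23.0% |
| 24 months | 104.4 | 92.4 | 11.5% |
| 60 months | 260.9 | 248.9 | 4.6% |

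These are minimum losses, because the choice cannot come before week 12.

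**Step 2: gap between arms.** Group A covers T − *s* weeks; B and C cover at most T − 12. Difference = (T − *s*) − (T − 12) = 12 − *s*.

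| Assumed delay *s* to surgery | Group A window longer by | Share of 24 months | Share of 60 months |
|---|---|---|---|
| 0 weeks | 12 weeks | 11.5% | 4.6% |
| 4 weeks | 8 weeks | 7.7% | 3.1% |
| 8 weeks | 4 weeks | 3.8% | 1.5% |
| 12 weeks | 0 weeks | 0% | 0% |

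With the choice made at week 12, the windows match only if surgery falls about 12 weeks after randomisation.

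**Step 3: the section 5.1 rule.** Every group starts at week 0. All have about 104 weeks to month 24 and 261 weeks to month 60, the gap is 0 weeks, and the start agrees with the utility baseline.

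**The case against.** The strongest reply is that two of the three places already agree on a common start, so the harm arises only if the one sentence in section 6.3.2 is followed. Section 2 calls cost utility a final point of interest, and it drives neither the primary endpoint nor the sample size. This stands, and it limits how far the point reaches. It does not remove the contradiction, because the outlying sentence stands where the diary and the ratio are defined.

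Four stronger readings are tempting, and the protocol does not support them:

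- **That standard-care costs as a whole are dropped, or that the missing weeks are the costliest.** Weeks 0 to 12 involve a BAHA on a headband and a CROSS on trial. Definitive BAHA surgery, its fitting and continued CROSS use come after the choice (section 5.1) and are captured even under section 6.3.2. Only test-phase costs are lost.
- **That 11.5% measures the bias.** It is calendar time in groups B and C to month 24. It is neither a share of cost nor the difference between arms.
- **That CI is bound to look too expensive.** Group A also loses costs before surgery, and its preoperative evaluation may fall there. The direction is likely with prompt surgery but is not established.
- **That collecting both HUI3 and EQ5D is a fault.** Section 6.3.2 does not say that two ratios will be reported, and the choice of base-case utility is commonly left to an analysis plan.

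It can also be said that HUI3 and EQ5D are not scheduled between baseline and month 6, so the first 12 weeks enter the QALYs only by interpolation, and that the protocol does not state where the area under the curve begins. Both are correct. The mismatch with the utility window therefore rests on the baseline being at randomisation, which is also why the common origin should be written down.

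**Conclusion.** The contradiction is real and stands in the current text: section 6.3.2 against sections 5.1 and 3. Following section 6.3.2 leaves at least 12 weeks of costs uncollected in groups B and C (11.5% of the time to month 24, 4.6% to month 60) and the interval from randomisation to surgery uncollected in group A. The cost window then differs between arms and from the randomisation-based utility data.

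The imbalance between arms is 12, 8 or 4 weeks for an assumed delay to surgery of 0, 4 or 8 weeks, and nil at about 12 weeks, taking the choice to be made at week 12. With prompt surgery it tends to overstate the incremental cost of CI. The protocol gives no unit costs, so no amount in euros can be derived.

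The point concerns the secondary cost-utility objective only. It deserves correction because the missing diaries could not be recovered at analysis.

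**What to change.** In section 6.3.2, replace the sentence on when the diary starts with the rule of section 5.1: the diary begins on the first day after inclusion in all three groups. Add one sentence stating that costs and QALYs both run from randomisation over the same horizon. Section 3 needs no change.

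The cost is a wording amendment. Groups B and C would keep the diary for about three months more than section 6.3.2 asks, and group A for the time up to surgery, but section 5.1 already asks this of both. The change should be made before diaries are issued; for subjects already started under the later rule, the uncollected period should be reported by arm.
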